**Figure 3 F3:**
[figure not shown]
Early design for a game based on the sit-to-stand exercise.

### Hypothesis

The home-based use of visualizations and multimodal games will be more effective for encouraging adherence to home rehabilitation programmes than standard care, thereby improving adherence to exercise, confidence and quality of life.

### Participants

Participants who have had injurious falls will be recruited from the NHS Greater Glasgow and Clyde community falls prevention programme (CFPP). Participants who have had non-injurious falls will be recruited from the Glasgow Housing Association Sheltered Housing Scheme. Recruitment will occur at the point where older adults at risk of falling are offered home exercise by the physiotherapists at the CFPP, who will hand out information sheets and explain the study to the potential participants. Interested participants who meet the inclusion criteria and have given informed consent will then be randomized into one of the groups involved in the trial.

### Sample size

This study is a pilot RCT and as such, no power calculation has been carried out. It is intended that the results obtained from this study will inform the design of a larger trial upon which a robust power calculation can be done based on adherence to exercise.

### Inclusion criteria

Participants will be included in the study if they are over the age of 65 years; have had a fall in the past 12 months; live in the community; are able to perform home exercise; are able to give informed consent, and can understand simple instructions using the English language (to understand instructions from visualizations/games).

### Exclusion criteria

Participants will be excluded from the study if they are unable to give informed consent; have major cognitive visual or aural impairments, or are unable to understand instructions in English (necessary to understand the instructions from the visualizations/multimodal games). Exclusion criteria 1 and 2 will be determined with assistance from the physiotherapists and falls experts within the falls service and from Scheme managers in the Sheltered Housing Schemes.

### Outcomes

The outcomes for this study are consistent with useful relevant studies in falls prevention. They include measures of compliance, and gait/balance performance, as well as the use of questionnaire-based health and quality of life evaluation tools, which provide a multi-factorial assessment of a person’s falls risk. All outcome measures will be assessed at the start and at the end of the 12-week trial.

#### Primary outcome measure

##### Adherence to exercise

All of the participants will be required to record their exercise sessions on paper using a series of tick boxes, detailing what exercises they did, how many times they did them, and on what day they did the exercises. The sensors used in the intervention groups will automatically log usage data, which will reflect the amount of exercise performed.

#### Secondary outcome measures

##### Variability in stride length, stride time and double support time (DST)

Stride length and stride time are measures associated with the distance between one foot at the start and at the end of one gait cycle, and the time taken to complete this cycle. DST is the amount of time that both feet are simultaneously planted on the ground, and is expected to be 10% of one gait cycle
[17]. The stride-to-stride variability in these measures has been shown to be a major predictor of falls risk in the elderly
[18]. These measures will be captured using the GAITRite system
[19].

##### Gait speed

This measure indicates how fast a person walks, and it is known to be associated with falls risk. For instance, there is a suspected higher risk of outdoor falls in fast walkers, and a higher risk of indoor falls in slow walkers. Gait speed in slow walkers is expected to improve with regular exercise
[20-22] and will be captured using the GAITRite system.

##### Timed up and go test (TUG)

The TUG test is one of the most commonly used clinical measures for assessing gait and balance in older patients. Patients rise from a chair, walk a distance of 3 metres, and then return to the chair while being timed with a stopwatch. Healthy older adults are expected to complete the task in less than 10 seconds. A time >14 seconds is known to be associated with a high risk of falling
[20,23].

##### Romberg’s test

Romberg’s test is a standing balance test used to diagnose proprioceptive, vestibular and visual disorders related to maintaining balance. Patients are required to stand with their feet together, eyes open and their hands by their sides for a period of time, usually a minute. The process can then be repeated with their eyes closed
[24]. A positive Romberg sign is issued when the subject fails to maintain the standing posture during these tests.

##### *The measure of balance confidence*(*CONFBal*) *scale*

The CONFbal scale is a 10-item scale used to assess self-efficacy and confidence in maintaining balance
[25,26]. Scores to the individual questions are assessed on a scale of 1 to 3 (1 = confident, 3 = not confident).

##### Falls efficacy scale international (FES-I)

The FES-I is a useful tool that measures physical and social activities, as well as the level of concern about falling during these activities, both indoors and outdoors. The level of concern is measured on a 4-point Likert scale (1 = not at all concerned,4 = very concerned)
[27-29].

##### Quality of life - EuroQOL (EQ)-5D and Short Form (SF)-12

These are useful commonly used questionnaire-based tools for the assessment of quality of life
[30-35].

### Equipment

#### Home use

This study will utilize small inertial sensors (developed by Glasgow Caledonian University) as the primary control mechanism for the software tools. These inertial sensors, which provide a relatively cheap, and accurate motion capture system, will be strapped to various limbs depending on the exercise required, and will translate the users’ movements into the relevant motion in the software. During the trial, user feedback through visualizations of movement, or games will be shown to the user on a television connected to a laptop computer.

#### Home assessment and training

The participants will be visited at the start of the trial by the chief investigator and a research nurse, who are both trained in environmental risk assessment. During this visit, the chief investigator will train the participants how to perform exercises using the visual feedback and games systems. Through usability studies that will be conducted prior to the start of the trial, it is intended that the best possible way to keep the training time to a minimum will be identified. This means that the visualization and games systems will be designed to be accessible and easy to use. The participants will be asked to perform an exercise session during the home visit to ensure that they understand how to use the systems properly. A handbook on the operation of the system will also be provided to the participants, with clear annotated diagrams highlighting the various components, as well as details on achieving the maximum benefits offered by the system. Furthermore, the participants’ homes will be assessed to ensure that there is enough space to perform the exercises in a safe manner. Both the chief investigator and the research nurse will also assess the environment in order to identify an appropriate location for the equipment (laptop computer and inertial sensors) through which the participants will interact with the visualization/games.

### Statistical analysis

For qualitative data, Likert scales will be used for some questions, and for the open-ended questions, thematic coding will be used. Quantitative data from the laboratory tests (baseline and outcome measures of gait and balance) will be analysed on an intention-to-treat basis. Statistical analyses will focus on the possible existence of differences in outcomes between the control and intervention groups using a two-way, repeated-measures analysis of variance (ANOVA).

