**Methods:**

A pllel-group pilot randomized controlled trial with 3 groups of participants will be conducted in the home for 12 weeks. Participants will include older adults who have been identified as at risk of falling (n = 48), over the age of 65, living in the community, and suitable for a home exercise intervention. The primary outcome is adherence to exercise. Secondary outcomes include: variability in stride length, stride time and double support time (DST); walking speed; Timed up and go test (TUG); Falls Efficacy Scale International (FES-I); CONFbal scale; Romberg’s test; and quality of life measures (SF-12 and EuroQol EQ-5D). Qualitative assessments on personal experiences with rehabilitation tools will be done before and after the trial.

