### Study design

The study will involve a three-arm, pllel-group randomized controlled trial (RCT) based in the community. Participants will provide written informed consent prior to taking part in the study. Randomization will be done using a computer-based number generator. Participants in all three groups will be allocated an intervention based on a 1:1:1 ratio (Figure
1). The trial will be carried out over a 12-week period.

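### With one baseline and one 12-week value, the planned two-way repeated-measures ANOVA is valid but less precise than ANCOVA adjusting for baseline

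*Protocol article*

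**What the plan says.** The Statistical analysis section of the Protocol article names one method for the quantitative comparison. It will examine "differences in outcomes between the control and intervention groups using a two-way, repeated-measures analysis of variance (ANOVA"). It does not say which term of that model is the treatment effect. The sentence before it concerns the laboratory gait and balance data, which "will be analysed on an intention-to-treat basis".

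The Outcomes section fixes the number of measurements: "All outcome measures will be assessed at the start and at the end of the 12-week trial". Each outcome with a pre-treatment value therefore has exactly one baseline and one follow-up value.

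The abstract gives the size of the trial, "older adults who have been identified as at risk of falling (n = 48"), and Study design gives equal allocation to three arms. Under Sample size the article states: "This study is a pilot RCT and as such, no power calculation has been carried out". It gives no effect size, standard deviation, baseline to follow-up correlation, significance level or loss to follow-up.

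**The concern.** Repeated-measures ANOVA suits several follow-up times whose pattern is itself of interest. Here there are two values, and the first precedes treatment. The two between-group terms then mean the following.

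- **Group-by-time interaction.** This compares the mean change between arms. It subtracts the whole baseline value whatever the correlation, which adds noise when the correlation is below 1.
- **Group main effect.** This compares the average of the baseline and 12-week values. Randomised arms have the same expected baseline, so this average carries only half of any treatment effect.

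The first is a legitimate treatment test, but it leaves precision unused. The second is not an estimate of the treatment effect. The plan speaks of differences between groups without naming the term, so it should make clear that the second is not meant.

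At about 16 per arm, precision is scarce. The trial is meant to inform a larger one, and tighter estimates for gait, mobility and questionnaire scores would serve that purpose.

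**Working it through.** The article gives no power or precision figure to reproduce. The check compares the two analyses on the same data.

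**Inputs from the article.** Total 48 (abstract); ratio 1:1:1 (Study design), so 48/3 = 16 per arm; two measurement times (Outcomes).

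**Assumed inputs.** Equal variance σ² at both times, set to 1; correlation r between 0.3 and 0.9; a true effect of 0.8 SD at 12 weeks for one intervention against control; two-sided 5% level; everyone measured twice.

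**Step 1: variance per participant.**
- Change score (the interaction test): σ² + σ² − 2rσ² = 2(1−r)σ².
- ANCOVA (residual variance after regression on baseline): (1−r²)σ² = (1−r)(1+r)σ².
- Ratio, ANCOVA to change score: (1−r)(1+r) / [2(1−r)] = (1+r)/2.

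| r | Change variance 2(1−r) | ANCOVA variance 1−r² | Ratio | Standard error of the change analysis larger by |
|---|---|---|---|---|
| 0.3 | 1.40 | 0.91 | 0.65 | 24.0% |
| 0.5 | 1.00 | 0.75 | 0.75 | 15.5% |
| 0.7 | 0.60 | 0.51 | 0.85 | 8.5% |
| 0.9 | 0.20 | 0.19 | 0.95 | 2.6% |

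The last column is √(2/(1+r)) − 1. In participants, the change analysis needs 2/(1+r) times as many for equal precision: 1/0.75 = 1.33 times at r = 0.5 and 1/0.85 = 1.18 times at r = 0.7.

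**Step 2: power for one contrast.** The noncentrality is 0.8 / √(V × 2/16), with V from the table. The reference is a noncentral t with 48 − 3 = 45 degrees of freedom for the change analysis and 44 for ANCOVA.
- r = 0.5: change 0.8/√(1.00 × 0.125) = 2.26, power 60%; ANCOVA 0.8/√(0.75 × 0.125) = 2.61, power 72%.
- r = 0.7: change 0.8/√(0.60 × 0.125) = 2.92, power 82%; ANCOVA 0.8/√(0.51 × 0.125) = 3.17, power 87%.
- r = 0.9: both about 99.9%.

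The lost degree of freedom is already in these figures and does not alter them at this rounding.

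**Step 3: the group main effect.** The average of the two values has expected treatment difference (0 + δ)/2 = δ/2, half the effect at 12 weeks.

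**Step 4: validity.** A simulation with three arms of 16 and an assumed 20% of 12-week values missing at random gave type I error of 0.050 to 0.056 for the change analysis and 0.050 to 0.058 for ANCOVA. Power of the three-group test, with both interventions 0.8 SD above control, was 0.50 against 0.62 at r = 0.5 and 0.74 against 0.79 at r = 0.7. Both methods used the same participants, about 38 of 48. The difference is one of efficiency, not of bias.

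**The case against.** The strongest reply is that this is a choice between two valid tests in a pilot without a power calculation. The gain depends on a correlation that the article does not give, and it almost vanishes near r = 0.9. The primary outcome, adherence during the programme, has no natural pre-treatment value, so it gains nothing. All of this is correct, and it limits the size and reach of the point. It does not remove the point, because the article plans between-group testing, already collects the baseline, and gives up nothing of substance by adjusting for it.

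Three stronger readings are tempting, and the article does not support them.

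- **That the ANOVA contradicts intention to treat.** A least-squares fit without imputation does use only people with both values. But the article nowhere says that incomplete cases are excluded, and rules for missing data are commonly left to a fuller plan. ANCOVA on complete cases would lose the same people.
- **That a mixed model with a common baseline mean would bring back those without a 12-week test.** With two time points and only 12-week values missing, its treatment estimate comes from the completers. In a simulated check with 10 of 48 missing, it equalled complete-case ANCOVA to five decimals (0.66673 and 0.69890 for the two arms).
- **That the trial will report the group main effect as its result.** For the same 0.8 SD effect, that would mean power of 25% at r = 0.5 and 22% at r = 0.7. The wording permits this reading but does not state it, and the interaction is the conventional treatment test in this design.

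**Conclusion.** The concern holds as a matter of efficiency. For continuous secondary outcomes measured at baseline and 12 weeks, the planned analysis amounts to a change-score comparison. Its variance is 2/(1+r) times that of ANCOVA: about 54% more at r = 0.3 (1/0.65), 33% more at 0.5, 18% more at 0.7 and 5% more at 0.9.

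The variance ratio assumes equal variances at the two times. The power figures also assume 16 fully measured participants per arm, an effect of 0.8 SD and a two-sided 5% level. Loss to follow-up would lower power under both methods, but would leave the variance ratio unchanged.

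Nothing here shows bias, an inflated error rate or a breach of the stated analysis population. The conclusion covers gait variability, gait speed, the timed up and go test and the questionnaire scores. It does not cover adherence or the Romberg sign, which is recorded as positive or negative.

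**What to change.** In Statistical analysis, replace the two-way repeated-measures ANOVA for the continuous secondary outcomes with an ANCOVA of the 12-week value on arm and the baseline value of the same measure. Report the adjusted difference of each intervention from control with its 95% confidence interval. This also settles which quantity is the treatment estimate, so that the group main effect cannot be mistaken for it.

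No further covariate is needed for this purpose. In particular, the article describes no stratification by recruitment source that would call for adjustment. Adherence and the Romberg sign keep their own analyses.

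The cost is one sentence of text and one degree of freedom per outcome. No new data are required.

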### Ethical approval

Ethical approval for this study was granted by the NHS Research Ethics Committee 3, Scotland, UK (Reference: 11/AL/0383).

## Discussion

A problem with adherence to exercise has been identified in community falls prevention as well as in research trials, and this is the basis for this study. Participants included in this study will be provided with tools that could potentially increase their motivation to perform home exercise, which in turn could help improve their gait, balance and mobility. In addition, the use of these tools could reduce their fear of falling (if present) and improve their quality of life. The multimodal games and visualizations also have the potential to help the participants understand why each of the exercises is important to their recovery and to assure them of the progress that they make during their rehabilitation.

The use of computers and inertial sensor technologies is relatively new to older adults at risk of falling (age 65 years and older). It was necessary to identify the major problems that they may face when using such technologies in the absence of a professional. Some of the most important barriers may include using the computer, strapping on and managing the inertial sensors (for example, charging the sensors), and successfully navigating their way around the software. In this project, seniors have been involved in the initial design and development of the visualizations, games and sensors. This user involvement process included: 1) involving older adults in design workshops to identify the limitations of standard home rehabilitation care (booklets); 2) determination of the requirements necessary to ensure that the proposed intervention tools were useful to them (visualizations and games), and 3) generation of concept ideas for the appearance and operation of these tools
[7,8]. It is the intention of this project to involve elderly users in the iterative design and modification of these tools in usability studies prior to the start of the randomized controlled trial. This will be done in order to ensure that these relatively new technologies are easy to use and manage by older adults in the home.

## Trial status

Recruitment for the trial started in October 2012, and will end in July 2013.

## Abbreviations

ANOVA: Analysis of variance; CFPP: Community Falls Prevention Programme; CONFBal: Measure of balance confidence; COPD: Chronic obstructive pulmonary disease; DST: Double support time; EQ: EuroQOL; FaME: Falls management exercise; FES-I: Falls efficacy scale international; NHS: National Health Service; RCT: Randomized controlled trial; SF-12: Short Form-12; TUG: Timed up and go.
